## Abstract

**Objective::**

To assess whether surface disinfection with organosilane in the intensive care unit reduces the occurrence of healthcare-associated infections.

**Methods::**

This multicenter, controlled, cluster-randomized trial includes 14 intensive care units in Brazil from November 2023 to December 2024. The local hygiene team of the included intensive care units will disinfect bed surfaces with organosilane or with usual care for 6 months, followed by a sequential crossover of another 6 months. The primary outcome is the incidence of healthcare-associated infections, specifically ventilator-associated pneumonia, central-line-associated bloodstream infections, and catheter-associated urinary tract infections. The secondary endpoints are the contamination of the environment by multidrug-resistant microorganisms (i.e., oxacillin-resistant *Staphylococcus aureus,* vancomycin-resistant *Enterococcus faecium,* carbapenem-resistant Enterobacter, *Pseudomonas,* and *Acinetobacter*), the incidence of specific infections (i.e., ventilator-associated pneumonia, central-line associated bloodstream infection, and catheter-associated urinary tract infection) and the cost of the patient's intensive care unit stay. We will enroll all adult patients admitted after the study begins in each participant's intensive care unit.

**Ethics and dissemination::**

The institutional review board of the coordinator center and each enrolled center approved the study protocol. We will disseminate the results in peer-reviewed journals and at scientific meetings, regardless of the study's outcome.

## INTRODUCTION

Healthcare-related infections (HAIs) are widespread events in intensive care units (ICUs). An international study to assess the prevalence of HAIs, involving 88 countries, showed that 12% of all patients admitted had an ICU-acquired infection, the presence of which was associated with higher mortality.^(1)^ A systematic review of 18 studies showed that admission to the ICU increases the odds of HAI acquisition by almost 4 times.^(2)^ In addition to increasing mortality, the acquisition of HAIs during an ICU stay may increase the length of hospital stay and, consequently, hospitalization costs.^(3)^

Contamination of hospital surfaces appears to play an important role in the transmission of HAIs. *Clostridium difficile*, methicillin-resistant *Staphylococcus aureus* (MRSA), vancomycin-resistant *Enterococcus,* and Gram-negative MR bacilli survive on surfaces for long periods.^(4,5)^ Several studies have shown that patients admitted to the ICU can acquire microorganisms from prior ICU bed occupants.^(6,7)^ Eradicating these pathogens is difficult with current environmental cleaning models. Even after adequate cleaning, environmental surfaces can quickly become contaminated again about 2 to 6 hours after the disinfection.^(8)^ Therefore, measures that can prolong the periods of suppression of microbial growth in the environment and thus reduce the occurrence of nosocomial infections may be a potential solution to this issue.

Organosilanes are a class of chemical substances composed of siloxane-based nanoparticles with antimicrobial properties. Organosilanes are stable in water and provide residual antimicrobial activity for surfaces that have already been cleaned using standardized procedures. Organosilanes do not affect microbial metabolism, which makes it difficult for resistance to develop. They produce a strong positive electrical charge, which breaks down the cell wall of microorganisms, acting against bacteria and fungi *in vitro.*^(9,10)^ To date, there have been few published studies evaluating the effects of organosilane.^(10)^ A randomized clinical trial carried out in a single ICU showed that organosilane-based cleaning reduced the number of colony-forming units by 65.9%. In comparison, traditional cleaning caused a reduction of only 35.1% over a 5-month study period.^(11)^ However, this study did not provide any data on the rate of patient infections. Therefore, the clinical impact of this intervention remains to be seen.^(12)^

This trial aims to assess whether surface disinfection with organosilane in the ICU reduces the occurrence of HAIs (i.e., ventilator-associated pneumonia [VAP], central-line-associated bloodstream infection [CLABSI], and catheter-associated urinary tract infection [CA-UTI]). Secondarily, it aims to assess whether surface disinfection with organosilane reduces surface colonization by multidrug-resistant organisms, whether it reduces specific HAIs (namely, VAP, catheter-associated primary bloodstream infection, and CA-UTI), and how the intervention impacts on ICU costs.

## METHODS

The study ORGanosilane for Surface CLEANing in Intensive Care Units (ORG-CLEAN) aims to assess whether surface disinfection with organosilane reduces the incidence of HAIs. The main characteristics of the ORG-CLEAN trial, according to World Health Organization (WHO) standards, are summarized in the synopsis table (Table 1).

**Table 1 t1:** Synopsis (World Health Organization trial registration data set)

Data category	Information
Primary registry and trial identifying number	ClinicalTrials.gov ID NCT05673226
Date of registration in primary registry	January 5, 2023
Secondary identifying numbers	PROADI 25000.013526/2021-13
Development agency/funding source	Brazilian Ministry of Health (Institutional Development Programme of the Unified Health System)
Primary sponsor	Brazilian Ministry of Health
Secondary sponsor	*Hospital Israelita Albert Einstein*
Contact for public queries	[name] E-mail: [contact] [contact]
Contact for scientific queries	[name] E-mail: [contact] [contact]
Public title	Organosilane for surface cleaning in intensive care units
Scientific title	Organosilane for surface disinfection in intensive care units: a cluster randomized controlled trial with crossover
Countries of recruitment	Brazil
Health conditions/problems studied	Healthcare-acquired infections, intensive care unit
Interventions	Comparator: Surface disinfection with organosilane Control: Usual surface disinfection
Key inclusion and exclusion criteria	Inclusion: ICU clusters (all patients aged 18 or over admitted after the start of the study) Exclusion: ICUs that use any organosilane formulation for surface disinfection
Study type	Intervention/cluster Allocation: randomization Intervention design: crossover Masking: open Purpose: reduction in healthcare-acquired infections
Date of first enrollment	November 6, 2023
Sample size	14 clusters, approximately 13,000 patients
Recruiting status	Recruiting
Primary outcome	Incidence of healthcare-acquired infections
Secondary outcomes	− Occurrence of contamination of environmental surfaces by multidrug-resistant microorganisms; − Occurrence of the following HAIs: ventilator-associated pneumonia, catheter-associated urinary tract infection, and central line-associated bloodstream infections; − Evaluation of the economic impact of using organosilane.
Ethics review	First approved by *Hospital Israelita Albert Einstein* Institutional Review Board on 20 December 2021 (CAAE 52639521.1.1001.0071) and in each participating center after that (supplementary file). *Hospital Israelita Albert Einstein* Institutional Review Board. [contact] E-mail: [contact]

ICU - intensive care unit; HAI - healthcare-related infections.

We used the Recommendations for Interventional Trials (SPIRIT) guidelines for this report.^(13)^ The final report will follow the Consolidated Standards of Reporting Trials (CONSORT) statement and its extension for cluster randomized trials^(14)^ and the Consolidated Health Economic Evaluation Reporting Standards 2022 (CHEERS 2022).^(15)^ The trial was registered with ClinicalTrials.gov (NCT05673226) before the inclusion of the first patient.

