#### Sample size

We based the sample size calculation on a baseline incidence of HAIs of 9.88%, as indicated by preliminary data from a sample of the IMPACT MR platform cohort study conducted from 2018 to 2020.^(23)^ Assuming 556 patients per unit over 6 months, with a within-cluster within-period correlation of 0.01, a within-cluster between-period correlation of 0.008, a significance level of 5%, and a power of 80%,^(24)^ the study required a total of 14 participating units to detect a relative reduction of 20.2% (equivalent to an absolute reduction of 2%) in HAI rates due to the intervention. The estimated total number of patients across all participating units is 15,558.

After establishing the initial 14 centers, consideration was given to include two additional centers, bringing the total to 16. If we included these additional centers in the sample size calculation while maintaining all other parameters constant, it would require 411 patients per cluster per period, resulting in a total of 13,138 patients. However, the two additional centers ultimately did not participate in the study.

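### Table 1 lists 14 ICUs with about 13,000 patients, but the sample size section requires 15,558 for 14 ICUs; the Table 1 size gives about 76% power, not 80%

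*Protocol article*

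**What the plan says.** Table 1 (Synopsis), in the row labelled Sample size, reads "14 clusters, approximately 13,000 patients".

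The Sample size section describes two designs with the same effect size, correlations, significance level and power:

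- **14 ICUs.** It starts from "Assuming 556 patients per unit over 6 months" and concludes that 14 units give 80% power. "The estimated total number of patients across all participating units is 15,558".
- **16 ICUs.** With two more centers and all else unchanged, "it would require 411 patients per cluster per period, resulting in a total of 13,138 patients". The section then says that these two centers did not take part.

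The Study setting section agrees on that last point: 16 ICUs were selected, and two withdrew after randomization and before recruitment began.

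**The concern.** The number of units and the number of patients go together: fewer units need more patients per unit. Table 1 takes its 14 units from one design and gives a patient total that fits only the other. The two totals for the same 14 ICUs differ by far more than rounding.

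Table 1 is presented as the WHO registration data set, so many readers will take the planned size from it. If about 13,000 patients are accrued, Table 1 says the target was met, while the Sample size section says the trial fell about one sixth short of what 80% power required. A null result would be read differently in the two cases.

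**Working it through.** **Inputs, all from the Protocol article**

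- Control risk p1 = 0.0988 and absolute reduction 0.02, so p2 = 0.0788 (Sample size).
- "a within-cluster within-period correlation of 0.01" and "a within-cluster between-period correlation of 0.008" (Sample size).
- Significance level 5% and power 80% (Sample size); two-sided tests (Statistical analysis plan).
- Two-period crossover, so each ICU contributes one cluster-period of m patients to each arm, and K ICUs give a total of 2Km.

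**Step 1: the totals**

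- 14 ICUs: 2 × 14 × 556 = 15,568, which agrees with 15,558 apart from rounding of m (15,558 / 28 = 555.6).
- 16 ICUs: 2 × 16 × 411 = 13,152, which agrees with 13,138 in the same way (13,138 / 32 = 410.6).
- Table 1: 13,000 / 28 = 464.3 per ICU per period, not 556.
- Shortfall: 15,558 − 13,000 = 2,558, and 2,558 / 15,558 = 16.4%.

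**Step 2: reproduce the protocol's two designs**

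Patients per arm without clustering:

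n = (1.960 + 0.842)² × [p1(1 − p1) + p2(1 − p2)] / 0.02² = 7.849 × (0.08904 + 0.07259) / 0.0004 = about 3,172.

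Design effect for a two-period cluster crossover:

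DE(m) = 1 + (m − 1) × 0.01 − m × 0.008.

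Clusters required: K = n × DE(m) / m, plus 2 as a small-sample allowance. The protocol does not state this allowance; it is inferred because it recovers both stated designs.

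| m | DE | n × DE / m | plus 2 | Protocol says |
|---|---|---|---|---|
| 556 | 2.102 | 11.99 | 13.99 | 14 |
| 411 | 1.812 | 13.98 | 15.98 | 16 |

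Solved the other way, 80% power needs m = 555.03 for 14 ICUs and m = 410.06 for 16, which round up to the stated 556 and 411.

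**Step 3: power at the Table 1 size**

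Standard error of the risk difference = √{[p1(1 − p1) + p2(1 − p2)] × DE / (m × K_eff)}, with K_eff = 14 − 2 = 12.

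- m = 464.3: DE = 1.919; SE = √(0.16163 × 1.919 / (464.3 × 12)) = 0.00746; 0.02 / 0.00746 = 2.681; power = Φ(2.681 − 1.960) = 76.4%.
- m = 555.6 (15,558 patients): DE = 2.101; SE = 0.00714; ratio 2.802; power = 80.0%.

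**Step 4: other formulas at 14 ICUs and 13,000 patients**

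| Method | Power at 13,000 | m needed for 80%: 14 ICUs | m needed: 16 ICUs | Matches 556 and 411? |
|---|---|---|---|---|
| Normal, two clusters held back | 76.4% | 556 | 411 | Yes |
| t test, 13 df (K − 1) | 76.3% | 560 | 412 | Nearly |
| t test, 12 df (K − 2) | 75.8% | 577 | 420 | Roughly |
| t test, 26 df (2K − 2) | 79.6% | 474 | 364 | No |
| Plain normal, no allowance | 82.5% | 411 | 326 | No |

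**Step 5: detectable effect**

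At m = 464.3 with 14 ICUs, the relative reduction detectable with 80% power is 21.1% by the formula of Step 2 (2.09 percentage points absolute), and 21.1% to 21.3% by the t tests on 13 and 12 df, against the stated 20.2%.

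**The case against.** The strongest reply is that this is a slip in a summary table. The Sample size section labels each total with its number of units, so a careful reader can resolve the conflict. The trial enrols every eligible adult over fixed periods and has no interim analysis, so neither total controls recruitment, and correcting the line changes neither who is enrolled nor the precision obtained. Table 1 itself makes no power claim. The final report will give confidence intervals, and a null result should be read mainly from those.

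Much of this is fair and limits the consequence, but it does not remove the contradiction. Three further points deserve an answer.

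- **Where 13,000 comes from.** The protocol does not say. That it carries over the 16-ICU total is an inference, resting on 13,138 being the only matching figure. It could be an expected accrual, but the row is labelled Sample size and nothing calls it that. If it is, the assumption of 556 patients per ICU no longer holds for the units taking part, and neither does 80% power.
- **Dependence on the formula.** A plain normal formula gives 82.5% at 13,000 patients. It also gives 85.7% for 14 ICUs with 15,558 and 85.0% for 16 ICUs with 13,138, so it is not how the protocol reached 80%.
- **Size of the effect.** A loss of about 3.5 points is modest. Changing the between-period correlation from 0.008 to 0.007 or 0.009 moves power at 556 per period from 80% to about 70% or 90%. That argues for proportion in describing the consequence, not for leaving two planned sizes in the document.

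**Conclusion.** The concern holds. For the same 14 ICUs the protocol gives two planned totals, about 13,000 and 15,558, and only the second matches its own calculation. That conflict is visible in the text and depends on no power formula.

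The power at the Table 1 size is about 76% (75.8% to 76.4% across the methods that come close to the protocol's figures), with a detectable relative reduction of about 21%. This rests on the stated risks and correlations, equal cluster-period sizes, and the inferred small-sample allowance.

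**What to change.** Make Table 1 and the Sample size section agree, in one of two ways:

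1. If the requirement stands, change the Table 1 entry to 14 clusters and approximately 15,560 patients (556 per ICU per period).
2. If about 13,000 is what the 14 ICUs are expected to accrue, label it as expected accrual, and state in the Sample size section that this gives about 76% power for the 20.2% relative reduction, or 80% power for about 21%.

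In either case, the 16-ICU total should not appear in the synopsis as the size of the 14-ICU trial. The registry record was not available for this review; if it carries the same pairing, it should be corrected too.

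The cost is a change of text. No patients, units or analyses are added. Under the second option, the stated power becomes slightly less favourable.

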### Study setting

We propose a cluster study with a crossover in ICUs participating in the IMPACTO MR platform.^(16)^ The research team initially selected 16 ICUs, but two ICUs withdrew from the trial after randomization and before initial patient recruitment.

### Eligibility criteria

We include all patients aged 18 or over admitted to the ICUs participating in this clinical trial. All the participating ICUs are already part of the IMPACTO MR platform. We excluded ICUs that use any organosilane formulation for surface disinfection.

### Randomization

Specific computer software generates randomization codes sequentially, stratified by ICU size (up to ten beds *versus* more than ten beds), in a 1:1 ratio, assigning ICUs to either the intervention or the usual disinfection group. We randomized each unit to perform either usual surface disinfection or organosilane disinfection for 6 months.

### Blinding

The hygiene personnel applying the intervention cannot be blinded, as they will know which product they are using for disinfection. However, the statistician responsible for analyzing the data will be blinded to the study intervention.

### Intervention and usual care

The professionals from the hygiene and cleaning teams of the participating centers and their leaders received remote online training, which was replicated several times by the coordinating center with the support of a specialist nurse from the study.

During the 6 months of the study intervention, the hygiene/cleaning team at the participating centers proceeds with the terminal cleaning of the vacant bed using detergent and then applies the organosilane to it, aerosolizing the room from the back to the door and from top to bottom. After this process, the person responsible for the application moistens the cloth with organosilane and then rubs it on highly touched surfaces, such as furniture (e.g., the bed, chair, bedside table, gauze panel, communication panel, IV stand, dining table, and other furniture). The hygiene team uses organosilane both in single-bed and multi-bed ICUs whenever there is a need for terminal cleaning of the bed when the patient is discharged. During the intervention period, the hygiene team completed a form for each terminal cleaning performed using organosilane. This form assessed the length of time the patient spent in the ICU, whether they were under precautions or isolation, the time of day, and the total time of completion of the process.

During the 6 months of usual care, the hygiene/cleaning team disinfects the beds and environment according to their established protocols, using standard products.

After a 1-month washout period, the units previously randomized to organosilane crossover back to their usual disinfection regimen, while the units randomized to usual disinfection will receive the organosilane intervention (Figure 1).

**Figure 1 f1:**

Trial timeline, interventions, and microbiological data collection.

### Outcomes

The primary outcome is the incidence of HAIs (i.e., VAP, CLABSI, and CA-UTI) during the 6-month study period, as diagnosed according to the criteria of the *Agência Nacional de Vigilância Sanitária* (ANVISA)^(17)^ (Table 2). The secondary endpoints are the contamination of the environment by multidrug-resistant microorganisms (i.e. oxacillin-resistant *Staphylococcus aureus,* vancomycin-resistant Enter*ococcus faecium,* carbapenem-resistant Enterobacter, *Pseudomonas* and *Acinetobacter*) at the end of each phase of the study; the incidence of each specific monitored HAI (VAP, CLABSI, and CA-UTI) and the cost of the patient's ICU stay.

**Table 2 t2:** *Agência Nacional de Vigilância Sanitária* diagnostic criteria for healthcare-related infections

Healthcare-associated infection	ANVISA diagnostic criteria
Ventilator-associated pneumonia	Patient with two or more consecutive days of invasive mechanical ventilation use with no underlying heart or lung disease ***AND*** One of the following findings on thorax imaging tests, whether new, persistent, or progressive: − Infiltrate − Opacification/consolidation − Cavitation − Pneumatocele ***AND*** At least one of the signs and symptoms: − Fever (temperature: > 38ºC), with no other associated cause − Leucopenia (< 4,000 cells/mm3) or leucocytosis (> 12,000 cells/mm3) − Altered level of consciousness, with no other apparent cause, in patients ≥ 70 years ***AND*** At least two of the signs and symptoms: − Appearance of a purulent secretion or a change in the characteristics of the secretion or increased respiratory secretion or increased need for aspiration − Apnea, tachypnea, dyspnea, or cough (new or worsening episode) − Auscultation with wheezing, snoring, or rales (new or worsening episode) − Worsening of gas exchange, desaturation, increased oxygen demand, or increased ventilatory parameters for at least 2 days
Central line-associated bloodstream infections	− Patient using a central catheter for more than two consecutive days ***AND*** − Presents a pathogenic bacterial or fungal microorganism identified from one or more blood samples obtained in a hemoculture ***OR*** − Identified genus and species, or at least genus, by validated non-culture-based test methods ***AND*** − The identified microorganism is not related to another infectious focus
Catheter-associated urinary tract infection	− Patient using an indwelling bladder catheter for more than two consecutive days ***AND*** − Has at least one of the following signs and symptoms, with no other recognized causes: − Fever (T > 38ºC) − Suprapubic pain or discomfort − Lumbar pain or discomfort − Hematuria − Urinary urgency − Increased urinary frequency − Dysuria ***AND*** − Positive urine culture with a maximum of two bacterial species with a colony count ≥ 10^5^ CFU/mL

ANVISA - *Agência Nacional de Vigilância Sanitária*; T - temperature.

### Data collection

#### Clinical data

We will extract patient data from the Epimed system,^(18)^ which provides data in a manner that makes it impossible to identify patients. The data collected consists of sex and age, ICU admission data (date of admission to the ICU and hospital, comorbidities, severity measured by the Simplified Acute Physiology Score 3 (SAPS 3) and Sequential Organ Failure Assessment (SOFA) scores, type of ICU admission (clinical, elective surgical, or unplanned surgical), reason for admission, use of a central venous catheter, mechanical ventilation, and indwelling bladder catheter; development of HAIs, microbiological cultures, vital status and date of ICU and hospital discharge.

#### Microbiological data

To assess environmental contamination, trained professionals from the participating centers collect samples from 30% of the beds in each participating ICU from the following surfaces: bed rails, monitor and infusion pump buttons, and dining tables or procedure tables. The professionals collect the samples using specific flocked swabs, pre-moistened with a sterile saline solution.

The collection of samples takes place before the start of the study, at the end of the first study period (month 7), and at the end of the second study period (month 14) (Figure 1). The professionals responsible for collecting the samples send them in a stabilizing solution (BiomeHub, Brazil),^(19)^ Brazil for ambient temperature transport, to the sample processing laboratory (BiomeHub, Brazil) within 30 days of collection.

The study laboratory analyzes the environmental microbiome, which identifies the set of microorganisms in each location. This technique consists of amplifying the V3/V4 hypervariable region of the 16SrRNA gene and preparing libraries for second-generation sequencing using the Illumina platform.^(19)^ Brazil The Quantitative Insights into Microbial Ecology software (QIIME2 v. 2020.11) is used to analyze the sequencing data. Furthermore, the study laboratory will perform an analysis of antimicrobial resistance genes relevant to the Brazilian scenario using real-time polymerase chain reaction.^(20)^ The remaining sample volume will be stored at -20ºC during the study period.

